**Figure 1 F1:**
[figure not shown]
CONSORT diagram of participation. CONSORT, Consolidated Standards of Reporting Trials.

### Randomisation and blinding

Cluster randomisation will use a block procedure for groups of 8–10 participants using computer-generated quasi-random numbers. Randomisation will be stratified by site, for between-site equity in the number of groups in each arm. The study will employ a single-masked design. This will be achieved by the allocation list being generated by a statistician independent from the research team. Study biostatisticians will remain masked until the database has been cleaned, a masked data review has taken place, and the database is ready for analysis.

### Intervention

#### Left Write Hook

Left Write Hook is delivered via 8× weekly 2-hour group-based sessions in a local gym/sports centre or community room. Sessions are led by two paid peer facilitators: a lead facilitator, assisted by an assistant facilitator, both of whom are survivors themselves. All peer facilitators are paid in line with industry rates for casually employed facilitators of exercise-based interventions. Each session has two components: expressive writing and trauma-informed non-contact boxing. An outline of the full programme, including session themes, is shown in table 1.

**Table 1 T1:** Outline of Left Write Hook programme

Week	Theme	Primary session goal
1	Grounding	Help people feel comfortable in the space and instil participants with a sense of purpose and feeling of being grounded.
2	Balance	Teach participants how to channel their emotions through the boxing. Create a safe environment for difficult emotions.
3	Expression (fluidity)	Help guide participants through difficult emotions and help them feel comfortable expressing themselves through writing and boxing. Give participants a healthy outlet.
4	Lightness	To have participants feeling lighter and more accomplished. To have participants feeling confident with their boxing.
5	Taking back your power	To have participants feeling confident in their boxing capabilities. To give participants the ability to harness their power.
6	Fighting Back	Give participants the building blocks to defend themselves. Have participants feel confident with weaving and pad work. Have the participants understand and express healthy aggression.
7	Rewriting narratives	To have participants take back their personal power
8	Imagining futures	To have participants be ready for the next steps in life once the programme ends, whether their next step is to return, become a facilitator or leave with a more positive outlook on life moving forward.

Writing prompts reflect the theme of each session.

The first hour involves participants writing to recovery-focussed prompts designed to reclaim their life narrative and encourage meaning-making (eg, ‘fighting back means…’), with the option of sharing with the group to encourage expression and validation. Writing prompts reflect the theme of each session. Participants are invited to write about anything that comes to mind for them in response to the writing prompts and session theme. While this means that they are not required to write about past trauma and may choose to write about any topic, participants do predominately choose to write about their experiences of trauma or its impact on them. Peer facilitators guide the expressive writing and also participate in the writing and sharing. Next, participants complete a 45-min trauma-informed non-contact group boxing session. Peer facilitators guide participants to connect with their body and locate an empowered state, carrying through the theme from the expressive writing to guide participants’ focus on stance, punch, direction and movement. Each session ends with 15 min of grounding and reflections. Details on how the principles of trauma-informed care are embedded within the programme are outlined in table 2.

**Table 2 T2:** Examples of trauma-informed considerations across interventions and research procedures

Programme element	Trauma-informed principle(s)^25^
*Intake*	
Use inclusive and easy to understand language	Empowerment, voice and choice
Provide clear and detailed information on what the programmes involve	Safety, trustworthiness and transparency
Collaborative decision-making with potential participants regarding programme suitability at this time	Empowerment, voice and choice
Establish confidentiality and safety regulations	Safety, trustworthiness and transparency
Let survivors choose to share or withhold	Empowerment, voice and choice
*Both Left Write Hook and boxing-only interventions*	
Female or gender-diverse facilitators	Empowerment, voice and choice
All facilitators trained in trauma-informed facilitation	Safety, trustworthiness and transparency
Venue selection (accessibility, private space, limiting mirrors, quiet break-away space)	Safety
Invitational facilitation style to promote agency and choice	Safety, empowerment, voice and choice
Facilitators complete in-person research assessments, not trial staff	Safety, trustworthiness and transparency
Sessions begin with an acknowledgement of country, which acknowledges the ongoing impact of generational and cultural trauma in colonised Australia	Cultural, historical and gender issues
Acknowledgement that boxing might activate discomfort	Safety, trustworthiness and transparency
Clear description of session structure at the beginning of each session	Safety, trustworthiness and transparency
Non-contact and non-violent approach to boxing	Safety
Modifications available and participants encouraged to go at their own pace	Empowerment, voice and choice; collaboration and mutuality
Focus on progress not performance	Empowerment, voice and choice
Build trust through consistency and established routines	Trustworthiness and transparency
*Left Write Hook only*	
Peer-led	Collaboration and mutuality; peer support
Cocreation of group values in week 1	Collaboration and mutuality
Facilitators write to prompts and share alongside participants	Collaboration and mutuality; peer support
Choice in writing prompts and activities	Empowerment, voice and choice
Invitation to locate healthy aggression	Empowerment, voice and choice
Non-censored space; group makes collaborative decision around what details are shared, and this is revisited throughout the programme	Empowerment, voice and choice; collaboration and mutuality

Trauma-informed principles as per Trauma-Informed Care in Behavioral Health Services, Substance Abuse and Mental Health Services Administration, 2014.

#### Active control: boxing-only

Participants randomised to control will complete 8× weekly group sessions of trauma-informed non-contact boxing, without writing and without a specific focus on empowerment, to control for the positive effects of exercise on self-efficacy. Each week, participants will complete a 45-min group boxing session, led by a boxing instructor (ie, intervention is not peer-led) at the same sites as the intervention arm. This replicates the type of trauma-informed exercise class that survivors could access in their local community. Boxing was selected as the exercise modality based on consumer input that identified it as the most acceptable exercise option for an active control, particularly in the context of consenting to randomisation. The control group therefore represents trauma-informed exercise options as usual, without three unique components of the Left Write Hook intervention: the peer-led nature of intervention, expressive writing and the focus on empowerment that links from the expressive writing to the trauma-informed non-contact boxing component to encourage expression through physical movement. Trauma-informed considerations for the boxing-only group are outlined in table 2.

#### Facilitator and participant support

Facilitators of both the Left Write Hook and boxing-only programmes are supported by fortnightly group supervision sessions with a clinical psychologist. The clinical psychologist is on call for facilitator and participant support during and after all sessions for both the intervention and control groups. They also offer debriefs to both facilitators and participants via phone call or Zoom on an ‘as needed’ basis. Left Write Hook facilitators additionally have access to a community of practice, facilitated through WhatsApp by the Left Write Hook charity. This community of practice is not monitored by the research team.

#### Champion training

Alongside the Left Write Hook intervention, we are assessing the implementation of a champion training programme (see figure 2 for overview of training components) for new Left Write Hook facilitators. Champions may train to perform one of three roles: lead facilitator, who holds enhanced qualifications; assistant facilitator, who primarily provides peer support and only holds basic qualifications or boxing coach, who has a boxing certificate and a group fitness bridging certificate (which are both completed externally), plus completed the trauma-informed boxing component of the Left Write Hook training programme. A lead or assistant facilitator can also act as a boxing coach (ie, deliver the boxing component of the intervention), if they have completed the appropriate certification. Certification is verified by Left Write Hook’s head of operations. Past Left Write Hook participants who have met these requirements are invited to enrol in a 6-week, self-directed online training course in Trauma-Informed Writing and Boxing Facilitation. The training course involves six online modules that guide prospective champions through the essential components of facilitating a Left Write Hook programme (module content outlined in figure 2). Modules are comprised of a mix of multimedia resources, educational videos, group discussion boards and assessments (multiple-choice questions, a digital portfolio, a statement of practice). At the completion of the training programme, collaborative discussion between Left Write Hook’s head of operations and champions evaluates readiness to act as a lead facilitator or whether beginning as an assistant facilitator is preferable. Champions become formal peer facilitators once programme requirements are complete (figure 2 placed here).

**Figure 2 F2:**
[figure not shown]
Flowchart of Champion Training Journey. CPR, Cardiopulmonary resuscitation.

### Positionality statement

 Our core research team is made up of predominately white, cisgender women, including clinical psychologists, researchers and experts by lived experience. Some team members draw on both lived and learnt expertise, though their primary roles in this study are grounded in academic and clinical perspectives. We acknowledge that these shared and divergent positionalities shape our approach to research, including study design, data collection, participant engagement and interpretation of findings.

### Patient and public involvement statement

With a focus on the coproduction of research, this trial has been designed to actively involve and empower adult survivors of gender-based violence. The intervention has been designed and is delivered by survivors. Moreover, the trial has been designed to build the capacity of consumers to take ownership of the Left Write Hook intervention and to use their experiences to support others. In addition to the Lived Experience co-lead, the research has been codesigned by a paid Lived Experience Advisory Group (LEAG), comprising eight individuals who have experienced gender-based violence, including both those who have and have not participated in the Left Write Hook programme. The LEAG convenes each quarter to provide their perspectives and guidance. Their contributions shape the study design (outcomes, measures), inform the structure of the champion training and coproduce questions for semistructured interviews with intervention participants, facilitators and site partners. A member of the LEAG also sits on the Trial Steering Committee. This partnership supports critical engagement with dimensions of experience not wholly reflected in the core research team, particularly related to power, race and representation.

### Outcome measurement by RE-AIM dimensions

Data will be collected from the site liaison, programme facilitators and participants, with data collected via surveys, interviews, in-person measures, site visits and website analytics. Evaluation has been mapped to the PRISM RE-AIM framework^62 66^ to understand the context for implementation and indicators of Reach (individual participation in intervention), Effectiveness (intervention’s impact), Adoption (participation of sites/staff in intervention), Implementation (degree to which intervention is delivered as intended) and Maintenance (long-term intervention effects and degree to which intervention becomes institutionalised) in community settings. Comprehensive information on outcome measurement and data collection time points is presented in the online supplemental materials (Table S1).

#### Context

Information about the implementation and sustainability infrastructure (eg, resource availability, funding) at each site will be collected via site visits and interviews with the site liaison, with data collected preimplementation and at the end of the trial period. Perceived barriers and facilitators to implementation will be assessed by the pragmatic assessment context tool^67^ completed by the site liaison at preimplementation.

#### Reach

Reach will be assessed at the individual level and reported in terms of the number of people who expressed interest in taking part in a programme and the number and demographic characteristics of the people that were assigned to a programme (ie, treatment or control), completed the assigned programme and withdrew from the assigned programme, as well as the programme facilitators. Data will be collected from the intake interview and the preintervention survey. Demographic characteristics collected will include: age, gender, caring responsibilities, language spoken at home, Aboriginal and Torres Strait Islander status, NDIS (National Disability Insurance Scheme) status, work status, health conditions, access to treatment and services. Participants and facilitators will be asked to report any changes in the modifiable factors at the 8-week and 12-week assessments.

#### Effectiveness

Evaluation of effectiveness will be conducted at the individual level (participant and facilitator, including withdrawals) to determine the impact of the programme on psychosocial and physical health outcomes. Participants who withdraw from the study will still be invited to complete outcome measures. All outcome measures are outlined in the online supplemental materials (Table S1). The primary effectiveness outcome is self-efficacy, measured by participant score on the General Self-Efficacy Scale.^53^ Secondary effectiveness outcomes will include complex PTSD symptoms, trauma-related cognition (trauma memory quality and post-traumatic cognitions) and indices of physical health (strength, flexibility, aerobic fitness and balance). Exploratory effectiveness outcomes include depression and anxiety, social connectedness, mental well-being, quality of life, health behaviours (exercise habits, smoking and vaping frequency, alcohol intake and use of health resources) and physical health (blood pressure, chronic pain, sleep quality and stress hormones). Self-report measures will be administered online via Qualtrics, either at home in a comfortable environment, via phone call with a member of the research team or at the gym/sports centre with the support of a facilitator. Due to logistical constraints, preintervention in-person assessments (physical fitness, blood pressure and hair sample) will be completed immediately prior to the commencement of the first Left Write Hook or boxing sessions at the sport centre by an unmasked programme facilitator, with responses recorded via Qualtrics. Hair samples indexing stress hormones (see online supplemental Table S1 for details) will be collected by the programme facilitator, trained in collection procedure by a member of the research team. Samples will be wrapped in aluminium foil and stored in a plastic ziplock bag and kept at room temperature in a locked cabinet until analysis, as per recommendations in the field.^68^

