**Methods and analysis:**

In this type II hybrid effectiveness-implementation cluster randomised controlled trial, we evaluate a novel peer-led intervention that combines expressive writing and trauma-informed boxing, Left Write Hook, against trauma-informed boxing alone—an intervention approach that is currently accessible in the community and has been shown to improve both mental and physical health. 20 clusters of 8–10 adults (n=150) with a self-reported history of child sexual abuse or other gender-based violence will be recruited in Melbourne, Australia, through health services and the community. Clusters will be randomly assigned to complete either 8× weekly group sessions of Left Write Hook (intervention) involving both expressive writing and trauma-informed boxing led by a trained peer facilitator, or 8× weekly group boxing sessions led by a trauma-informed boxing facilitator (control). Implementation will be evaluated against the PRISM Reach Effectiveness Adoption Implementation Maintenance (RE-AIM) framework. The primary effectiveness outcome is change in self-efficacy from preintervention to postintervention (8 weeks). Secondary effectiveness outcomes are changes in symptoms of complex post-traumatic stress disorder, trauma-related cognition and indicators of physical fitness (strength, flexibility, aerobic fitness and balance). Assessment will be completed online or over the phone with a member of the research team at preintervention (0 weeks), postintervention (8 weeks) and at 1 month following completion of the intervention (12 weeks). The primary implementation outcome is the fidelity of the train-the-champion implementation strategy for intervention training and delivery, and the secondary implementation outcome is adoption of the intervention and training delivery.

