
### Procedure

To determine eligibility, potential participants complete an intake interview with a clinical psychologist prior to enrolment in the trial. All enrolled participants will complete assessments at preintervention (0 weeks), postintervention (8 weeks) and at 1 month following the completion of the intervention (12 weeks). Self-report assessments can be completed at home or on the phone with a member of the research team. In-person assessments are taken by the programme facilitator immediately prior to the first session and immediately following the final session. Detailed information about the methodology and timing of assessments is outlined in figure 1. Eligible participants will not have to pay for the Left Write Hook or boxing-only programmes. Left Write Hook is currently accessible in the community (delivered via a survivor-led charity) through a suggested ‘pay what you feel’ donation of up to AUD$450 to the Left Write Hook charity. Participants also receive a AUD$20 Giftpay voucher for each of the three online assessments they complete. Those in the boxing-only condition will be offered participation in the Left Write Hook programme at the end of the trial.

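### The self-reported primary outcome may be completed at the gym with a facilitator's support, a mode absent from the abstract and Procedure, and the masking statement rests on list generation although only biostatisticians are stated to be masked

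*Protocol article*

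**What the plan says.** All references are to the protocol article.

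- **Outcome.** Effectiveness: "The primary effectiveness outcome is self-efficacy, measured by participant score on the General Self-Efficacy Scale". Sample size targets a 3-point difference between arms in mean change to week 8.
- **Modes of completion, Effectiveness.** Self-report measures are administered through Qualtrics at home, or "via phone call with a member of the research team or at the gym/sports centre with the support of a facilitator". The sentence is not limited to particular measures or time points.
- **Modes of completion, elsewhere.** Procedure: "Self-report assessments can be completed at home or on the phone with a member of the research team". Abstract: "Assessment will be completed online or over the phone with a member of the research team". Neither mentions the gym or a facilitator for self-report.
- **Who is at the venue.** Procedure has the programme facilitator take the in-person measures just before the first session and just after the last. Effectiveness describes the facilitator who takes the preintervention in-person measures as unmasked.
- **Facilitators by arm.** Left Write Hook is led by two paid survivor peers who write and share alongside participants. The control is led by a boxing instructor and is not peer-led.
- **Masking.** Randomisation and blinding: "The study will employ a single-masked design", followed by "This will be achieved by the allocation list being generated by a statistician independent from the research team" and then "Study biostatisticians will remain masked until the database has been cleaned".
- **Stated limitation.** Strengths and limitations concedes unmasked assessment only for the in-person physical measures.

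**The concern.** General self-efficacy is a subjective scale, answered by people who know which programme they attended. That cannot readily be changed in this comparison. Who is present when they answer can be changed. The gym route permits completion with support from someone who probably delivered the programme, and the participant's relationship with that person differs by arm by design. The goals of several Left Write Hook sessions (feeling confident, taking back power) also lie close to what the scale asks about. If participants answer differently in that company, the shift need not be equal in the two arms, and it would enter the primary treatment difference directly.

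The masking statement does not make this visible. Having an independent statistician generate the list protects the sequence; it masks nobody who gives or collects an outcome. A reader who sees the trial called single-masked, with a limitation confined to the physical measures, may think the primary outcome better protected than it is.

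**Working it through.** **1. The sections side by side**

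| Section | Home or online | Phone with research team | Gym with facilitator support |
|---|---|---|---|
| Abstract | yes | yes | not listed |
| Procedure | yes | yes | not listed |
| Effectiveness | yes | yes | yes |

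The GSES is a self-report measure, so the third column applies to it, including at week 8.

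**2. Who is stated to be masked**

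- Biostatisticians: masked until the database is ready for analysis.
- Facilitators taking in-person measures: unmasked (stated for the preintervention measures).
- Participants: no masking stated.
- Research staff taking phone assessments: not stated.

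**3. The plan's own figure, to fix the scale**

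Inputs from Sample size: difference 3, SD 5.6, two-sided 5%, power 80%, intraclass correlation 0.02, groups of 8 (64 per arm in 8 groups).

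- Individually randomised: n = 2 × (1.960 + 0.842)² × 5.6² / 3² = 54.7, so 55 per arm.
- Design effect: 1 + (8 − 1) × 0.02 = 1.14.
- 55 × 1.14 = 62.7, so 63 per arm, or 64 in eight whole groups of 8. This reproduces the stated 128.

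Using 5.6 as the SD of the change implies a pre-post correlation of 0.5, because the change variance is 2 × 5.6² × (1 − r). The article does not state that correlation.

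Standard error of the treatment difference: 5.6 × √(2 × 1.14 / 64) = 1.06 points.

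**4. Illustration of possible size (assumed inputs)**

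The article gives neither the uptake of the gym route nor any reporting shift. Let s be the share using the route at week 8, taken as equal in both arms, and b the between-arm difference in reporting shift among them. The spurious treatment difference is s × b. The type I error is that of a two-sided 5% normal test whose mean is displaced by s × b / 1.06.

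| s | b (points) | s × b | Share of 3-point target | Type I error |
|---|---|---|---|---|
| 10% | 1 | 0.10 | 3% | 5.1% |
| 25% | 1 | 0.25 | 8% | 5.6% |
| 25% | 2 | 0.50 | 17% | 7.6% |
| 50% | 2 | 1.00 | 33% | 15.7% |
| 100% | 2 | 2.00 | 67% | 47% |

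If b is zero, so is the bias. If b is negative, it works against Left Write Hook and costs power. A shift present equally at weeks 0 and 8 would cancel in the change score. The case of interest is a shift that appears only once the facilitator is known.

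**The case against.** - **The facilitator's identity is inferred.** The text says a facilitator, without naming the arm, and does not define support, which may mean a device, a quiet room or help with the form. This stands. The inference is still well founded, since facilitators run the sessions and take the in-person measures at the venue.
- **The sections may not strictly conflict.** Neither the abstract nor Procedure calls its list exhaustive, Procedure is permissive in wording, and Qualtrics at the gym is still online completion. This also stands: it is an inconsistency to reconcile, not a flat contradiction.
- **Analyst masking is real.** So the label is imprecise rather than empty. What remains is that list generation is given as the means of masking, and that the article does not say who is unmasked.
- **Bias that differs by arm is not shown.** Both arms have facilitators trained in trauma-informed practice, over eight weekly sessions, and peer status might encourage candour as easily as it raises scores. A reader might infer that the primary result will be biased in favour of Left Write Hook by a definite fraction of the target effect. The documents do not support that: they show a risk, with no direction and no size.
- **The alternative has weaknesses too.** A telephone interviewer can also prompt socially desirable answers, and support at the venue may keep some participants in follow-up. Both are fair. But staff who did not run the groups have no programme relationship that differs by arm, and the phone route already exists.
- **There is a trauma-informed rationale.** Table 2 explains why facilitators rather than trial staff take the in-person assessments. It does not say that the reason extends to questionnaires, which can be completed at home.

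**Conclusion.** The point holds as an avoidable risk to the primary outcome and an imprecise masking statement. Two things rest on the text alone: the Effectiveness section opens a facilitator-supported route for the GSES that the abstract and Procedure do not list, and the only people stated to be masked are the biostatisticians. That the supporting facilitator belongs to the participant's own programme is a strong inference. That any reporting shift would differ by arm is plausible but not demonstrated.

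The size cannot be derived from the documents. Under the assumed inputs it runs from negligible (0.1 point, type I error 5.1%) to serious (2.0 points, 47%), depending on uptake and shift. The sample size reproduces and is not in question. The change is worth making because it costs little, and the masking wording needs correcting whatever the uptake.

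**What to change.** 1. Make the abstract, Procedure and Effectiveness list the same modes. For the GSES, at least at weeks 8 and 12, provide for completion without a programme facilitator: self-completed online, or by the existing phone option with research staff not involved in the groups.
2. Record the mode of completion for each GSES form, and report a sensitivity analysis by mode. Treat it as supportive only: mode at follow-up is chosen after randomisation, so leaving out assisted forms can itself introduce bias.
3. Reword Randomisation and blinding to say that participants, facilitators and in-person assessors are unmasked and the statisticians masked; state whether phone assessors are masked; and describe independent list generation as a safeguard of the sequence.
4. Extend the limitation on unmasked assessment to the self-reported primary outcome.

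The cost is revised wording, a few more phone assessments and possibly slightly more missing data. Recruitment opened in September 2024 and is expected to run until June 2026, so assessments still to come can benefit. The modes available would then change during the trial, which is a further reason to record mode and to report the date of the change.
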